**Methods:**

A hybrid type I effectiveness-implementation trial will be conducted. A cluster randomized controlled trial will be used to assess the effectiveness of `Saga Stories in health talks´ in 42 CHC centers across six regions in Sweden. `Saga Stories in health talks´ consists of material for CHC nurses to use to facilitate the health talk with both the child and parent(s) and is complemented with take-home material. Parent and child dyads are recruited (*n* = 450) from participating CHC centers when they attend their 5-year routine visit. The intervention group receives the health talk using Saga Stories and take-home material, whereas the control group receives the standard health talk. The primary outcome is parental self-efficacy to promote healthy diet, physical activity, and screen time behaviours in their child and secondary outcomes include children’s intake of key dietary indicators and screen time. All outcomes are assessed at baseline and 2-months post-intervention. The implementation outcomes that will be assessed are: acceptability, appropriateness, feasibility, satisfaction, usage, fidelity, adoption, and sustainability (assessed quantitatively and qualitatively).

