### Effectiveness evaluation

#### Study design, recruitment, and participants

`Saga Stories in health talks´ is a cluster randomized controlled trial which will be conducted in six regions throughout Sweden (Dalarna, Norrbotten, Värmland, Västernorrland, Västra Götaland, and Örebro). The intervention group receives the health talk using Saga Stories and take-home material, whereas the control group receives the standard health talk. Eligible families are provided with oral and written information regarding the study from their CHC nurse at the routine five-year check-up. If the accompanying parent consents to participate they will scan a QR code to sign the informed consent using BankID (a secure digital signature) and directly after they will fill in the baseline questionnaire. To be included in this study, the accompanying parent needs to be able to understand and read Swedish sufficiently well in order to provide informed consent and partake in the Saga Stories health talk. There are no exclusion criteria. This study is reported according to the SPIRIT 2013 statement [12] and Table 1 shows a trial participant timeline.

**Table 1 Tab1:** Participant timeline according to SPIRIT

	STUDY PERIOD			
	Enrollment	Allocation	Post-allocation	Close-out
Time point	0	0	2 months	2 months
	5-year routine visit			

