##### Sample size

We calculated the sample size required to achieve a statistical power of 80% to detect a four-point difference in parental self-efficacy between the two treatment groups. The power was for a Wald test of the coefficient of the group variable in linear random intercept model where the 6-month change in outcome is the dependent variable and the group indicator is the only covariate. The linear random-intercept model included a center-specific normal random intercept, which accounted for the within-center stochastic dependence of the data. The estimated sample size was obtained by generating 1000 pseudo-random Monte-Carlo samples under an assumed intra-center correlation of 0.03 and the two specified group differences. The assumed fixed regression coefficients and the regression residual variance were estimated using unpublished parental self-efficacy data from the MINISTOP trial [16]. A total of 368 parent child dyads (*n* = 184 per arm) are needed. Assuming a 20% drop-out rate [16, 17], a minimum of 450 children will be recruited, i.e., 225 per group.

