##### Statistical analyses

All analyses will be conducted according to the intention-to-treat method. The primary analysis will be completers only, as long as the missing data is considered missing completely at random. Missing data will be imputed using multiple imputations with chained equations [18]. To contrast differences in parental self-efficacy, dietary intake, and screen time between treatments, we will use linear random-effects models, specifying the CHC center as a random effect to account for clustering. The models will be estimated unadjusted and adjusted for child age (continuous) and sex (boy vs. girl). Interaction analyses will also be conducted to investigate if the interventional effect differs with regards to the participating parents’ age, education status, country of birth, and body mass index (BMI).

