One of the main strengths of this trial is the type I hybrid-design which allows us to evaluate both effectiveness and implementation outcomes. Collecting both effectiveness and implementation outcomes simultaneously has the potential to expedite the translation of research results into routine care [10]. Additional strengths of this study include the randomized controlled trial design (effectiveness evaluation) and large sample size accounting for clustering on the CHC level. Furthermore, public health interventions are conventionally developed using a top-down approach and do not include the end-users in the development process [25]. A recent systematic review and meta-analysis on international healthcare literature found that co-creation is thought to improve health related outcomes such as health-promoting behaviours [26]. In this case CHC nurses requested material that they could use to facilitate their health talks with families. Thereafter, relevant stakeholders were brought on board to create the material together with the nurses. Thus, even though Saga Stories for use in health talks (i.e., a working tool plus take-home material) was not created using a specific theoretical background it was developed utilizing co-creation through involving end-users (CHC nurses and parents), stakeholders (Generation Pep, dieticians, and pediatricians), and academic researchers in an iterative process. A limitation of this study is that only parent and child dyads that can speak and read Swedish sufficiently well will be included in this study, which will limit the generalizability of the results. In Sweden, approximately 25% of children have a migrant background [27] and at visits within CHC anyone that does not speak Swedish has the right to an interpreter. A study by Ersson et al. [8] with Swedish CHC nurses has previously found that communication through an interpreter may affect how messages are delivered. As the Saga Stories in health talks intervention’s focus is the health dialogue between the nurse, parent(s), and child we have only included Swedish speaking participants to ensure the intervention is delivered as intended. This study is further limited through the use of self-reported outcomes for the effectiveness evaluation. The baseline questionnaire, including questions on both parental self-efficacy for promoting healthy lifestyle behaviours as well as the child’s dietary intake and screen time, will be evaluated at the beginning of the routine five-year check-up at baseline. This, coupled with the lack of blinding of nurses and parents could lead to social desirability bias. The research team carefully discussed theses limitations during the study design process; however, there was no way to avoid these and thus they should be taken into consideration when interpreting the results. It is also important to highlight that researchers with expertise in both clinical and implementation research have designed this trial together in order to optimize the hybrid design. This is important, as using hybrid designs can be challenging due to the use of different constructs, theories, and concepts between clinical and implementation researchers [10].

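### The effectiveness models leave out the baseline value of each outcome, which is collected from every parent, and so give up precision whether change or the 2-month score is analysed

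*Protocol article*

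**What the plan says.** - **Models.** The Statistical analyses section says of self-efficacy, dietary intake and screen time: "we will use linear random-effects models, specifying the CHC center as a random effect to account for clustering". It then gives the covariates: "The models will be estimated unadjusted and adjusted for child age (continuous) and sex (boy vs. girl"). The baseline outcome is in neither version.
- **Baseline data.** The abstract states: "All outcomes are assessed at baseline and 2-months post-intervention". Under Study design, recruitment, and participants, the parent signs consent and "directly after they will fill in the baseline questionnaire". The Discussion places that questionnaire at the start of the visit and describes it as "including questions on both parental self-efficacy for promoting healthy lifestyle behaviours as well as the child’s dietary intake and screen time". The baseline value therefore precedes the health talk and is a legitimate covariate.
- **Power model.** The Sample size section targets "a statistical power of 80% to detect a four-point difference in parental self-efficacy between the two treatment groups", using a random-intercept model in which "the 6-month change in outcome is the dependent variable and the group indicator is the only covariate", with "an assumed intra-center correlation of 0.03". It arrives at 368 dyads, 184 per arm.

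**The concern.** The baseline value of the same questionnaire would ordinarily be the best available predictor of the 2-month value. The plan collects it and then adjusts for child age and sex instead. Every child is seen at the five-year visit, so age probably varies little, although the article gives no age distribution.

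Two things are at stake:

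- **Precision.** The trial is sized at only 80% power.
- **Chance imbalance.** Forty centres remain, 22 against 18, and families consent after their centre has been allocated, through nurses who know the allocation. Some baseline difference between arms is plausible even though randomisation was stratified by region and centre size.

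**Working it through.** **Inputs from the protocol article:** difference 4 points, power 80%, intra-centre correlation 0.03, 368 evaluable dyads, 42 centres randomised, 40 remaining (22 and 18), 450 recruited with 20% drop-out.

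**Assumptions, because the article does not give them:** two-sided alpha 0.05; rho mainly 0.5 to 0.7, with 0.3 and 0.8 shown as well; the same proportional variance reduction at centre and individual level.

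**Step 1: the plan's own figure.** The SD is not stated, so 368 cannot be reproduced independently. It can only be inverted.
- Dyads per centre: 368/42 = 8.76.
- Design effect: 1 + (8.76 - 1) × 0.03 = 1.233.
- Effective number per arm: 184/1.233 = 149.2.
- SD of change: 4 / [(1.960 + 0.842) × sqrt(2/149.2)] = 12.33.

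With 40 centres the result is 12.27. By construction, SD 12.33 returns 80% power for an unadjusted change score.

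**Step 2: variances.** Let s² be the variance of the score at one time point.
- Change score: 2s²(1-rho).
- 2-month score alone: s².
- 2-month score adjusted for baseline: s²(1-rho²).

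Adjusted against change gives (1+rho)/2. Adjusted against the 2-month score alone gives 1-rho². The first is below 1 for any rho below 1, the second for any non-zero rho.

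**Step 3: numbers.** The last two columns take the change score to have 80% power at 368.

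| rho | (1+rho)/2 | 1-rho² | Dyads for 80% power, adjusted | Power at 368, adjusted |
|---|---|---|---|---|
| 0.3 | 0.65 | 0.91 | 240 | 93.5% |
| 0.5 | 0.75 | 0.75 | 276 | 89.9% |
| 0.6 | 0.80 | 0.64 | 295 | 87.9% |
| 0.7 | 0.85 | 0.51 | 313 | 86.0% |
| 0.8 | 0.90 | 0.36 | 332 | 84.0% |

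**Step 4: remaining centres and expected completers.** 450 × 0.8 = 360 completers, or 9 per centre: 198 and 162. The design effect is 1 + 8 × 0.03 = 1.24. Non-centrality for change is 4 / [12.33 × sqrt(1.24 × (1/198 + 1/162))] = 2.75, power 78.5%. Dividing by sqrt((1+rho)/2) gives 88.8%, 86.7% and 84.7% at rho 0.5, 0.6 and 0.7.

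**Step 5: simulation check** (22 and 18 centres, 9 dyads each, intra-centre correlation 0.03, 3000 replicates per rho). At rho 0.3, 0.5 and 0.7 the variance ratio was 0.66, 0.75 and 0.86 for adjusted against change, and 0.91, 0.77 and 0.52 for adjusted against follow-up only. These agree with the formulas.

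**Step 6: chance imbalance.** A 1-point baseline difference carries an error of rho points into a follow-up-only estimate and -(1-rho) points into a change-score estimate. At rho 0.5 the simulated values were +0.49 and -0.51, against -0.02 after baseline adjustment.

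**The case against.** The strongest reply is that the Sample size section already uses change from baseline in the same family of models. Analysing unadjusted change is exactly what was powered, it is valid under randomisation, and the higher power would be a bonus rather than the repair of a shortfall. That stands, and it limits the point to efficiency. It does not remove the point: a change score is still less precise than baseline adjustment for any rho below 1, and the power text concerns self-efficacy only.

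Four stronger readings are tempting, and the article does not support them.

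- **Baseline imbalance goes uncorrected.** That would be true only if the 2-month score were modelled alone. A change score subtracts the imbalance and, through regression to the mean, over-corrects it.
- **The treatment estimate is biased.** Under randomisation it is not biased on average. The costs are precision and an error conditional on the imbalance that occurs. If recruitment after allocation selects different families, baseline adjustment helps only as far as the measured baseline captures the difference.
- **The omission leaves the trial underpowered.** The 78.5% in Step 4 comes from 360 rather than 368 completers and from unequal arms, not from the covariate list. Nor does a follow-up-only model always lose to change: the two have equal power at rho 0.5, and follow-up only does better below that.
- **Not naming the dependent variable or the primary model is an error.** A condensed article may leave that detail to the full protocol or analysis plan. The covariate list is different, because the article states it outright.

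**Conclusion.** The point holds as a loss of precision. The stated covariates leave out a predictor that is already collected for every outcome, and including it improves precision under either dependent variable.

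For self-efficacy the gain over a change score is about 15-25% of the variance for rho 0.7 to 0.5, or power of roughly 85-90% instead of about 80%. The direction is secure. The size is not, because rho and alpha are assumed and the SD of about 12.3 is back-solved rather than stated. The same variance factors apply to fruit and vegetables, sweet beverages and screen time, each with its own rho, but the power figures do not carry over to them. The validity of the trial is not in question. The change is worth making because it costs almost nothing.

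**What to change.** State the primary model as the 2-month outcome regressed on arm and the baseline value of the same outcome, with a random intercept for CHC centre. Apply it to self-efficacy, fruit and vegetables, sweet beverages and screen time, each with its matching baseline value. Keep the unadjusted and the age- and sex-adjusted models as supportive analyses.

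The cost is a sentence or two of analysis text. No new data and no larger sample are needed. The change should be recorded before anyone analyses outcomes by arm.

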#### Randomization and blinding

Forty-two CHC centers with 1-7 nurses per center were randomly assigned to the two treatment groups (22 CHC centers in the intervention and 20 in the control group). To ensure balance, we stratified the randomization by geographical regions and center size. Two CHC centers dropped-out before the trial was initiated due to high absenteeism because of the COVID-19 pandemic. Therefore, there is 22 CHC centers in the intervention group and 18 in the control group. Due to the nature of the trial, CHC nurses and participants cannot be blinded; however, outcome assessors are blinded to the treatment allocation of the participating families.

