#### Outcome measures

##### Primary outcome

Parental self-efficacy regarding the parent’s own ability to promote healthy lifestyle behaviours in their five-year old child is the primary outcome. This is assessed using an electronic version of the validated `Parental self-efficacy for promoting healthy dietary and physical activity behaviours in their children´ questionnaire. This questionnaire includes 16 questions divided into three factors (i.e., self-efficacy for promoting healthy dietary behaviours in children, self-efficacy for limit-setting of unhealthy dietary or physical activity behaviours, and self-efficacy for promoting healthy physical activity behaviours) [14]. This questionnaire will be filled in online by the same parent (i.e., the parent that accompanied the child to the five-year check-up) at baseline and post-intervention (i.e., two months after the five-year check-up).

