##### Secondary outcomes

A modified version of the Swedish National Board of Health and Welfare’s survey regarding health behaviours [15] is used to assess dietary outcomes. The amount of fruits and vegetables are assessed as the average number of standardized portions per day over the past month, and the intake of sweet beverages as the average frequency per day. The amount of time spent watching screens (e.g., phones, tablets, TV, and computer) is assessed in minutes per day on a typical day that the child is at home and not at pre-school.

At baseline, the accompanying parent will also complete a brief electronic demographic questionnaire which includes questions regarding their age, sex, and socioeconomic position as well as their child’s date of birth, sex, country of birth, weight, and height (measured at the five-year check-up).

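### The primary outcome belongs to the parent, but the prespecified adjusted model contains only the child's age and sex; adding parent covariates already collected would be a cheap improvement

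*Protocol article*

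**What the plan says.** All references are to the protocol article.

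- **Primary outcome:** the parent's "own ability to promote healthy lifestyle behaviours in their five-year old child is the primary outcome". The same parent completes the questionnaire at baseline and two months later.
- **Statistical analyses:** linear models with a random effect for centre serve self-efficacy, dietary intake and screen time alike. On covariates: "The models will be estimated unadjusted and adjusted for child age (continuous) and sex (boy vs. girl".
- **Secondary outcomes:** the baseline demographic questionnaire is one "which includes questions regarding their age, sex, and socioeconomic position", where these refer to the accompanying parent.
- **Statistical analyses, on effect modification:** "Interaction analyses will also be conducted to investigate if the interventional effect differs" by parent age, education, country of birth and BMI. This is the only stated analytic use of parent traits. Parent sex enters no stated analysis.
- **Randomization and blinding:** 42 centres were allocated, and "we stratified the randomization by geographical regions and center size". Two control centres left before the start, so 22 and 18 remain. Nurses and participants are not blinded.
- **Study design, recruitment, and participants:** families hear of the study "from their CHC nurse at the routine five-year check-up".

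**The concern.** The adjusted model contains no characteristic of the person whose outcome is analysed. Every child is seen at the five-year visit, so child age probably varies little (no SD is given) and can explain little of a parent's self-efficacy.

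Two things are at stake. First, only 40 centres carry the randomisation and no parent trait was a stratification factor, so chance imbalance in parent traits is possible and the stated adjustment cannot absorb it. Second, unblinded nurses approach families after their centre has been allocated. The arms could then differ systematically in which parents enrol, and randomisation of centres does not protect against that. The article states the adjustment set explicitly, so this is a comment on a choice made, not on detail left to an analysis plan that is not shown.

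**Working it through.** **Step 1: the outcome scale.** The Sample size section gives 368 dyads (184 per arm), 80% power, a difference of 4 points and an intra-centre correlation of 0.03. It gives no SD, so 368 cannot be reproduced independently. I solved for the SD that yields it, assuming a two-sided 5% test:

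- Dyads per centre: 368/42 = 8.76. Design effect: 1 + 7.76 × 0.03 = 1.233.
- SD = 4 / [(1.960 + 0.842) × √(2 × 1.233/184)] = 12.3. With 40 centres the design effect is 1.246 and the SD is again 12.3.
- Implied standard error of the group difference: 4/2.80 = 1.43 points.

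The power model analyses change, so this is the SD of change, and the correlations below are with the analysed outcome on that scale.

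**Step 2: how large a chance imbalance could be.** Assume half of parents are highly educated, 180 completers per arm (450 × 0.8 / 2) and a centre-level ICC for education between 0.05 and 0.20. None of the education figures is in the article.

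Var(difference in share) = 0.25 × [ICC × (1/22 + 1/18) + (1 − ICC) × 2/180]

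| Education ICC | SD of difference | P(gap of 10 points or more) |
|---|---|---|
| 0.05 | 6.2 percentage points | 0.11 |
| 0.10 | 7.1 | 0.16 |
| 0.20 | 8.5 | 0.24 |

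Stratification by region is ignored here and could lower these figures. A 10-point gap in a 50% trait is 0.10/0.5 = 0.2 SD of that trait.

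**Step 3: what a given imbalance does to the estimate.** Shift = r × 12.3 × d, where r is the trait's correlation with the analysed outcome and d its imbalance in SDs.

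| d | r = 0.1 | r = 0.2 | r = 0.3 | r = 0.4 |
|---|---|---|---|---|
| 0.2 | 0.25 | 0.49 | 0.74 | 0.98 |
| 0.3 | 0.37 | 0.74 | 1.11 | 1.48 |

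Equivalently, if high education were worth 3 to 8 points (assumed), a 10-point gap would shift the estimate by 0.10 × 3 = 0.3 to 0.10 × 8 = 0.8 points. That is 8% to 20% of the 4-point target, or 0.2 to 0.6 of a standard error.

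**Step 4: bias and precision under randomisation alone.** I simulated 22 v 18 centres, 368 completers, a true difference of 4 and a trait ICC of 0.03 to 0.20, with 2000 runs per setting. Estimation was by difference in means and by least squares with the covariate, as a simplification of the random-intercept model.

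- Without the parent covariate, the mean estimate lay between 3.96 and 4.05 in every setting, so there is no bias.
- Adjustment lowered the empirical standard error by less than 1% at r = 0.1 (for example 1.443 to 1.433), and by 8% to 15% at r = 0.4 (1.447 to 1.328; 1.551 to 1.322).

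**The case against.** The strongest reply is that nothing here is an error. Centres are randomised, the unadjusted estimate is unbiased, and its standard error already carries chance imbalance. That stands, and Step 4 confirms it. A reader might infer that the planned estimate is biased or that the arms are unbalanced; the article shows neither.

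Three further objections also stand.

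- **Change scores.** If the analysis uses change, as the power model does, or adjusts for baseline self-efficacy, a parent trait that acts on the level of self-efficacy largely drops out. Only traits that predict change still matter. The Statistical analyses section does not say which applies, so this protection can be neither assumed nor excluded.
- **Effect modification is not prognosis.** A reader might infer that the investigators expect parent age and education to predict the outcome because both are tested as modifiers. An interaction test asks whether the treatment effect differs by the trait, not whether the trait predicts the outcome.
- **The child covariates have a purpose.** The same models serve children's diet and screen time, for which child age and sex are reasonable covariates. They should not be called wrong.

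It can also be said that selective enrolment by unblinded nurses is a separate problem that three demographic variables will not cure. That is right for unmeasured differences. It does not remove the benefit for measured ones. Finally, drop-out related to education can be addressed in the planned multiple imputation, so I give that argument no weight here.

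**Conclusion.** The point holds as a modest, inexpensive improvement. The adjusted model omits every characteristic of the person on whom the primary outcome is measured, although relevant ones are collected. Under randomisation alone the loss is precision and conditional accuracy: negligible if parent traits barely predict the analysed outcome, and up to about 15% of the standard error if the correlation reaches 0.4. A 0.2 SD imbalance would move the estimate by roughly 0.25 to 1 point of a 4-point target.

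If enrolment differed between arms in measured parent traits, shifts of that size would be systematic, and the stated adjusted model could not correct them. The article gives no evidence that this has happened.

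The sizes rest on assumed correlations, ICCs and education share, a two-sided 5% test and the back-solved SD of 12.3. A reader might also conclude that the unadjusted model should be demoted. The article does not support that: the sample size was built on a model with treatment group alone, and which model leads is a trade-off that this point does not settle.

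**What to change.** Before outcome data are examined by arm, extend the prespecified adjusted model to include the accompanying parent's education (or socioeconomic position), age and sex, alongside child age and child sex. Keep the unadjusted model as planned. State how each covariate is coded and how missing covariate values are handled.

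The cost is wording, three or four degrees of freedom out of about 360 completing dyads, and the missing-value rule. No new data are needed if education is part of the socioeconomic items; the article does not list it separately, so this should be confirmed. Report the chosen parent traits by arm at baseline, and note that adjustment for them does not remove selective enrolment on unmeasured traits.
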